### Determination of sample size

Whist a cohort OPAT study showed 100% cure, and another Singapore study failed to show any mortality from KLA [3,8], studies from Taiwan estimate a mortality of approximately 10% [4,10]. Given the inherent selection bias in the OPAT study, we estimate that overall 95% of patients will meet the primary endpoint of clinical cure in the control arm. The non-inferiority margin has been set at an absolute difference of 12% in the primary efficacy endpoint. This figure is justified because of the significant gains from use of oral antibiotics in terms of convenience and cost. The required sample size for a non-inferiority test for two binomial populations, with one-sided type 1 error 0.025, power 0.8, and non-inferiority margin 0.12, is 64 (in each arm) by use of the one-sided *z*-test with continuity correction. Assuming an attrition rate of 15%, a total of 152 patients would need to be recruited over two years.

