An economic analysis will be performed. Admission costs will be obtained by searching the hospital’s data systems. Information retrieved will include diagnoses, tests, procedures and so on, for the period that participants are inpatients. The price of the specific antibiotics dispensed to each participant will be obtained from the hospital pharmacy database system. Following discharge, direct and indirect costs of all study related medical or non-medical healthcare utilization will be tracked via patient diaries and recordkeeping, inclusive of travel costs, days of work lost and the value of caregiver time. No discounting of costs will be necessary given the time span. The direct and indirect costs associated with the alternative treatment arms used will be calculated per patient at 12 weeks. The costs will be summarized using mean and median values and presented according to treatment arm. The primary cost-effectiveness ratio to be calculated will be the total incremental cost per clinical cure at 12 weeks between the two groups. The Student’s *t*-test will be used to compare the incremental cost effectiveness ratio (ICER) as well as mean costs between the two treatment groups. The bootstrap technique will be used to obtain confidence intervals around the estimated ICER. We will generate an empirical sampling distribution for the ICER using trial data by generating 1,000 independent samples of 100 cost and effect pairs from both the groups’ data drawn with replacement and calculating the ICER each time. We will then report 95% bias-adjusted confidence intervals for the ICER. Anticipating that actual cost and resource-use data is likely to be missing, we will impute values for the missing cases if necessary. The analysis will be performed using costs computed from both analytical perspectives. We also anticipate potential uncertainty around some values and assumptions made for unit costs. In such instances, sensitivity analysis will be performed to further explore the robustness of our results to the baseline assumptions that are made.

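### Secondary economic analysis: the t-test on the ICER cannot be run, bootstrap samples of 100 match no planned sample size, and a bias-adjusted interval on the ICER scale will not be interpretable

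*Protocol article*

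**What the plan says.** All the methods at issue are in the economic paragraph of the protocol article's Statistical analysis section.

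- **Definition.** The primary ratio "will be the total incremental cost per clinical cure at 12 weeks between the two groups".
- **Test.** A Student's t-test "will be used to compare the incremental cost effectiveness ratio (ICER) as well as mean costs between the two treatment groups".
- **Interval.** The sampling distribution of the ICER comes from "1,000 independent samples of 100 cost and effect pairs", drawn with replacement from the data of both groups. The text does not say whether 100 is per arm or in total. The authors will then "report 95% bias-adjusted confidence intervals for the ICER".

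Two other sections supply the context. Determination of sample size gives 64 per arm, raised to 152 in total for 15% attrition, and states that "we estimate that overall 95% of patients will meet the primary endpoint of clinical cure in the control arm". It gives no cure rate for the oral arm. Study endpoints lists overall cost, from payer and societal perspectives, among the secondary endpoints.

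**The concern.** The paragraph names specific methods, so this is not detail left to a fuller plan, and nothing elsewhere in the article corrects it. Three separate problems arise.

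1. A two-sample test needs a set of values in each arm. The ICER has none: it is one number that uses both arms at once.
2. An ordinary bootstrap reflects the sampling error of the trial only if each resample has the size of the data it stands for. A fixed 100 does not.
3. A ratio whose denominator can be positive, negative or zero does not order outcomes. A negative ICER can mean cheaper and better or dearer and worse; a positive one can mean dearer and better or cheaper and worse. Sorting such values and reading off limits, with or without bias adjustment, puts opposite conclusions next to each other.

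At stake is the economic result. The trial intends to use it in arguing for a more cost-effective strategy, and cost is one of the two gains, with convenience, cited to justify the 12% margin.

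**Working it through.** **Inputs.** From Determination of sample size: control cure 0.95, margin 0.12, one-sided type 1 error 0.025, power 0.80, 64 per arm, 15% attrition, 152 in total. From Randomization: 1:1 allocation. From Statistical analysis: resample size 100.

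**Reproducing the plan's own figure.** The oral-arm rate is not given, so 0.95 in both arms was tried.

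- Exact binomial power of the one-sided z-test (unpooled variance, continuity correction 1/n) is 0.753 at n = 63 and 0.807 at n = 64. Scanning upward from n = 50, 64 is the first value to reach 0.80.
- Attrition: 64 / 0.85 = 75.3, rounded up to 76 per arm; 2 × 76 = 152.

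Both stated figures are reproduced. Other versions of the calculation under equal rates give 52 (no correction) and 68 (Fleiss-type correction). Equal cure is therefore the reading that fits, but it is an inference.

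**1. The t-test.** ICER = (mean cost, oral − mean cost, control) / (cure proportion, oral − cure proportion, control). Every term needs both arms. No arm and no patient has its own ICER, so the two-sample test has no data. Mean cost does have patient-level values in each arm, so the same test on mean costs is sound.

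**2. Resample size.** The figure 100 equals none of 64, 76, 128 (2 × 64) or 152 (2 × 76). For a mean-like statistic, resampling m from n without rescaling multiplies the bootstrap spread by sqrt(n/m):

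| Reading of 100 | n = 64 per arm | n = 76 per arm |
|---|---|---|
| 100 per arm (m = 100) | sqrt(64/100) = 0.80, 20% too small | sqrt(76/100) = 0.87, 13% too small |
| 100 in total (m = 50) | sqrt(64/50) = 1.13, 13% too large | sqrt(76/50) = 1.23, 23% too large |

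A simulation with assumed lognormal costs (log-SD 0.8, 400 trials, 1,000 resamples each) gave the same four ratios for the interval on incremental cost.

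**3. The denominator.** With 95% cure in both arms the expected difference is 0. Its standard error is sqrt(2 × 0.95 × 0.05 / n), which is 0.039 at n = 64 and 0.035 at n = 76. Exact binomial probabilities:

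| Oral / control arm size | Oral cures less | Exactly equal | Oral cures more |
|---|---|---|---|
| 64 / 64 | 41.8% | 16.4% | 41.8% |
| 76 / 76 | 42.5% | 15.0% | 42.5% |
| 65 / 63 | 43.4% | 0.14% | 56.5% |
| 77 / 75 | 43.9% | 0.04% | 56.0% |

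Exact equality depends on equal arm sizes. The uncertain sign does not.

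Sensitivity to the inferred oral rate, at 64 per arm: with true oral cure of 93%, 97% or 90%, the less likely sign still has probability 25%, 21% or 10%.

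In the same simulation, with correctly sized resamples, about 87% of trials had bootstrap denominators of both signs with more than 2.5% on each side. Correcting the resample size therefore does not cure the third problem.

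**The case against.** The strongest reply is about reach. The paragraph also gives mean and median costs by arm and a valid t-test on mean costs, so whether oral treatment saves money can be answered without the ICER. That stands. A reader might infer that the whole cost-effectiveness analysis is invalid, or that the 12% margin loses its support. The article does not bear that out: the margin rests on convenience as well as cost, and on no ICER.

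A second reply concerns the numbers. It is tempting to turn the sqrt(n/m) factors into coverage of the planned interval. They hold for mean-like quantities. The plan bootstraps only the ICER, and no coverage was computed for its bias-adjusted interval, so none is claimed here. Likewise, the 15-16% chance of an undefined ICER holds only if the arms are exactly equal. Unfinished blocks within strata, or attrition, can easily make them unequal, and the chance then falls to 0.04% at 77/75. The sign problem remains.

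Third, equal cure is not stated, and the economic analysis population is not named. Missing costs may be imputed, and cure is imputed for dropouts in the ITT set, so 76 per arm may be closer than 64. Both points are fair, which is why ranges are given. Neither rescues a resample of 100.

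Finally, a condensed article may leave a cost-effectiveness plane or net-benefit analysis to the full plan. Their absence is not the fault found here; they appear only as replacements for a stated method that does not work.

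**Conclusion.** The point holds for a secondary economic endpoint and should be corrected. The primary non-inferiority analysis does not depend on it.

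- The t-test on the ICER cannot be carried out. This needs no assumption.
- The resample size of 100 is wrong under either reading. The direction of the error stays open because the text does not say what 100 counts. The sizes computed above rest on the planned arm sizes and on mean-like statistics.
- The planned ICER interval will probably not be interpretable at any resample size. This rests on the inferred 95% cure in both arms, and it weakens but does not disappear if oral cure is a few points higher or lower.

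**What to change.** In the economic paragraph of Statistical analysis:

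1. Delete the t-test on the ICER and keep it for mean costs.
2. Replace the fixed 100 with resampling of cost-effect pairs, with replacement, within each arm at that arm's observed size.
3. From those resamples, report incremental cost with its confidence interval beside incremental cure with its confidence interval. Express joint uncertainty as incremental net monetary benefit over a stated range of values per cure, or on the cost-effectiveness plane, in place of the bias-adjusted interval for the ICER.
4. The ICER point estimate may still be reported. Its reporting should not depend on whether the cure difference is significant.

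The cost is a change of wording, a few lines of code and slightly more analysis, with no new data. The downside is that there will be no single interval for the ICER. The change should be made before cost data are analysed by arm, so that the method is not chosen after the results are seen.

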### Objectives

The primary objective is to compare the rate of clinical cure after four weeks of IV antibiotics to early step-down to oral antibiotics in patients with *Klebsiella pneumoniae* liver abscess, with clinical cure determined at Week 12 post randomization, and defined as CRP < 20 mg/l, plus absence of documented fever ≥ 38°C in the preceding seven days, plus most recent abdominal imaging showing that the maximal diameter of the abscess has reduced. The main secondary objective is to compare the rate of clinical response between the two study arms, with clinical response determined at Week 4 post-randomization, and defined as per clinical cure. Other secondary objectives are to compare the rate of the following during the study period, between the two study arms (assessed at 12 weeks): all cause mortality; unplanned readmission for any cause; unplanned need for drainage; metastatic complications; recrudescent or breakthrough *K. pneumoniae* bacteremia; need to escalate antibiotics due to worsening infection or secondary infection; vascular catheter complications. Additionally, to compare the length of hospital stay (from the date of randomization to the end of inpatient stay), length of time the subject requires medical leave following hospital discharge (censored at 12 weeks), total cost, subject quality of life (QoL), and adherence to study drug between the two study arms.

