Safety endpoints include: need to stop study drug due to toxicity; toxicity as defined by Common Terminology Criteria for Adverse Events version 4.03 [17]; all adverse events (occurrence of adverse events up to 12 weeks post randomization or 30 days post last study dose if later than 12 week visit); serious adverse events (occurrence of serious adverse events at any time during the study period, whether or not they are thought to be related to the study drugs); need to escalate antibiotics due to worsening infection or secondary infection at any point between randomization and Week 12; vascular catheter complications at any point between randomization and Week 12.

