### Statistical analysis

Data from all sites will be pooled for analysis. Descriptive statistics summarizing clinical observations data (for example, demographics) will be presented according to treatment arm. Continuous variables will be summarized using mean and standard deviation. Categorical variables will be summarized using the number of observations and percentages. All statistical analyses will be performed using SAS Version 9.3 or higher (SAS Institute Inc. [name]; [contact]; [contact]). Statistical analysis and programming support will be provided by the Singapore Clinical Research Institute (SCRI).

An intention-to-treat (ITT) population set is defined as all randomized patients. The treatment group of patients in the ITT set is the planned treatment group, that is, according to the randomization list planned prior to the study commencement. A per protocol population is defined as all randomized patients who have taken at least one dose of study treatment and has the primary endpoint measured. The treatment group of patients in the per-protocol population is according to the treatment actually received. Patients will be assigned to the group as per the first dose received of the study treatment. If patients are issued the incorrect study treatment, they should continue on this treatment and not switch. For example if a patient was randomized to oral antibiotics but the first treatment they received after randomization was IV antibiotics they should continue on IV antibiotics. Statistical analysis for safety data and compliance will be carried out on an as-treated basis. This is the same as the per protocol population but without the requirement that the primary endpoint is measured. An as-treated set is defined as all randomized patients who have taken at least one dose of study treatment. The treatment group of patients in the as-treated set is according to the treatment actually received.

Demographic characteristics (age, gender and so on) and other baseline characteristics (for example, clinical measures taken at baseline) will be summarized by appropriated descriptive statistics according to randomization arm, that is, frequency and percent for categorical variables; mean, median, standard deviation and minimum/maximum for continuous variables.

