The analysis of safety endpoints will be on the as treated population. Numbers and percentages needing to stop study drug due to toxicity will be summarized between the two treatment arms; as will the numbers and percentages of reported clinical symptoms of moderate/severe grade (by body systems). Numbers and percentages of patients with at least one adverse event up to 12 weeks post randomization or 30 days post last study treatment (whichever is last) will be tabulated by treatment group and details of the event will be summarized. The numbers and percentages of serious adverse events will be tabulated by treatment group and the details will be summarized. Numbers needing to escalate antibiotics due to worsening infection or secondary infection at any point between randomization and Week 12 will be compared between arms using the Fisher’s exact test and the Clopper and Pearson CI will be calculated.

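### Antibiotic escalation is a between-arm secondary objective but is tested as a safety endpoint, by first dose received and not by randomized arm (minor)

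*Protocol article*

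**What the plan says.** Four places in the protocol article bear on this endpoint.

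- **Objectives.** A list opens with "Other secondary objectives are to compare the rate of the following during the study period, between the two study arms (assessed at 12 weeks". It includes "need to escalate antibiotics due to worsening infection or secondary infection; vascular catheter complications", alongside mortality, readmission, unplanned drainage, metastatic complications and bacteremia.
- **Study endpoints.** The secondary endpoint list keeps mortality, readmission, drainage, metastatic complications and bacteremia but omits escalation. The safety list that follows includes "need to escalate antibiotics due to worsening infection or secondary infection at any point between randomization and Week 12", and catheter complications.
- **Statistical analysis, safety paragraph.** It opens with "The analysis of safety endpoints will be on the as treated population" and ends with a formal comparison: "Numbers needing to escalate antibiotics due to worsening infection or secondary infection at any point between randomization and Week 12 will be compared" by Fisher's exact test, with a Clopper-Pearson interval.
- **Statistical analysis, populations.** "An as-treated set is defined as all randomized patients who have taken at least one dose of study treatment". It is tied to the per-protocol rule: "This is the same as the per protocol population but without the requirement that the primary endpoint is measured". Under that rule, "Patients will be assigned to the group as per the first dose received of the study treatment". The worked example is a patient randomized to oral who first receives IV, stays on IV and is analysed as IV.

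**The concern.** Grouping by treatment received suits drug toxicity and catheter complications, which depend on exposure. Escalation is different. In part it asks whether the infection was controlled under the assigned strategy, and that question is best answered by comparing the groups as randomized.

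The label matters here because it decides the analysis set. Once escalation sits under safety, its test leaves out patients who took no dose and allows a patient to change arm according to the first drug given. Allocation is not blinded, and participants are inpatients who may already have had up to seven days of effective IV treatment. If an oral-randomized patient is kept on IV because of concern about their condition, that patient is counted as IV. If such patients need escalation more often than others, the shift lowers the oral rate and raises the IV rate. In a non-inferiority trial of oral therapy, that is the direction to guard against.

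**Working it through.** **1. Which analysis set applies.** The Objectives and Study endpoints sections name no analysis set. The paragraph on other binary endpoints prescribes Fisher's test without naming a population. Only the safety paragraph attaches a set to escalation, and it is the as-treated set. The text therefore gives one set, reached through the safety label. Escalation is also the only item in that paragraph with a formal between-arm test. Drug stops for toxicity, symptoms, adverse events and serious adverse events are summarized or tabulated.

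**2. Who changes group under the first-dose rule.**

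| Patient randomized to oral | As-treated group |
|---|---|
| Takes oral first, later worsens and is escalated | Oral |
| Given IV before any oral dose | IV |
| Takes no study treatment | Excluded |

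Only the second and third rows depart from the randomized comparison.

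**3. Arm size for an illustration.** Determination of sample size gives 64 per arm and 15% attrition: 64 / (1 − 0.15) = 75.3, rounded up to 76, and 2 × 76 = 152, as stated. (The 64 also reproduces: exact enumeration of a continuity-corrected one-sided z-test with unpooled variance, 95% cure in both arms and a 12% margin gives power 0.807.)

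**4. Illustration on assumed counts.** The article gives no escalation rate and no expected number of first-dose mismatches, so every event count below is an assumption. Let *a* and *b* be escalations in the oral and IV arms as randomized, and *r* the number of escalated oral-randomized patients who had IV first. The as-treated difference is

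(*a* − *r*)/(76 − *r*) − (*b* + *r*)/(76 + *r*).

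| *a* v *b* | *r* | Oral | IV | Difference (points) | Fisher p |
|---|---|---|---|---|---|
| 12 v 4 | 0 | 12/76 = 15.8% | 4/76 = 5.3% | 10.5 | 0.06 |
| | 1 | 11/75 = 14.7% | 5/77 = 6.5% | 8.2 | 0.12 |
| | 2 | 10/74 = 13.5% | 6/78 = 7.7% | 5.8 | 0.30 |
| | 3 | 9/73 = 12.3% | 7/79 = 8.9% | 3.5 | 0.60 |
| 8 v 4 | 0 | 8/76 = 10.5% | 4/76 = 5.3% | 5.3 | 0.37 |
| | 1 | 7/75 = 9.3% | 5/77 = 6.5% | 2.8 | 0.56 |
| | 2 | 6/74 = 8.1% | 6/78 = 7.7% | 0.4 | 1.00 |
| | 3 | 5/73 = 6.8% | 7/79 = 8.9% | −2.0 | 0.77 |

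Each escalated patient moved takes about 2.3 to 2.5 points off the difference. With *r* = 0 and every patient dosed as randomized, the two analyses are identical.

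**5. The shift can go the other way.** If the one patient moved did not escalate, the 12 v 4 table becomes 12/75 = 16.0% v 4/77 = 5.2%, a difference of 10.8 points against 10.5 as randomized. The bias favours oral only if the patients moved escalate more often than those who stay.

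**The case against.** Several points on the other side stand.

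- A reader might infer that early failures of oral treatment are shifted into the IV arm. The first-dose rule does not do that: one oral dose fixes the patient in the oral group, whatever follows. A patient given IV first has not failed oral therapy.
- The remaining route is narrow. Study drug is to start immediately after randomization. The exclusion criteria remove patients who cannot take oral medication and those with unresolved hypotension or tachycardia or on inotropes or ventilation. The rule is introduced for patients issued the wrong treatment. Deliberately keeping a sick patient on IV is plausible in an open trial, but the article does not describe it.
- A reader might also infer two competing analysis sets for one endpoint. Only one is stated. A safety endpoint may serve a secondary objective, and catheter complications carry the same double listing without harm.
- Escalation includes secondary infection, which can be a complication of treatment. A safety label for the composite is therefore defensible.
- Any p-value shown depends on the counts chosen. A starting table of 8 v 1 gives p = 0.034, which one moved escalator changes to 0.096 (7/75 v 2/77). Yet 7 v 1 gives p = 0.063 with nobody moved.

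These points limit the size of the problem. They do not make first dose received the better grouping for an outcome that partly measures failure of the assigned strategy.

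**Conclusion.** The point holds, as a minor one. Escalation is stated as a secondary comparison between arms, dropped from the secondary endpoints, and tested in the as-treated set because it is labelled safety. An outcome that is partly treatment failure is thus not compared as randomized in an open-label trial. The article fixes this set explicitly, so it is a stated rule to change and not a gap left to an analysis plan.

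The effect depends on two unknowns: how many oral-randomized patients receive IV before any oral dose, and how often they escalate. The number may be zero, in which case this route changes nothing. If some are moved and they escalate more often than the rest, the comparison tilts towards oral. The 2.3 to 2.5 points per escalated patient moved rest on assumed counts and are no forecast. The primary conclusion does not depend on this endpoint: non-inferiority on clinical cure must be shown in both the intention-to-treat and per-protocol populations. The sample size does not change either.

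**What to change.** Classify the whole escalation endpoint, worsening and secondary infection together, in the same way in Objectives, Study endpoints and Statistical analysis. Listing it with the secondary endpoints would match the Objectives. Make the Fisher comparison and its interval in all randomized patients by randomized arm, and keep the as-treated table as supportive. Leave drug toxicity and catheter complications in the as-treated set. Do not split worsening infection from secondary infection, since that would leave half of the composite without an assigned analysis.

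The cost is a few words in three sections and one extra table. No additional data or patients are needed.
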